## Abstract

**Background:**

In Chinese medicine, the mental focus and emotional stability of acupuncturists are key to optimal clinical outcomes. Many renowned acupuncturists utilize Traditional Chinese Qigong practices to enhance their concentration and emotional regulation abilities. Nevertheless, the existing literature lacks comprehensive evidence addressing this matter.

**Methods:**

This study will enroll 99 acupuncturists and randomly allocate them to one of three groups: Baduanjin, aerobic exercise, or a waiting-list control. The Baduanjin group will undertake 24 weeks of training, with three one-hour sessions weekly. The aerobic group will engage in brisk walking for the same duration and frequency. The control group will not receive any specific training. Assessments of emotion regulation, attention, cognitive functions, finger sensation, and athletic ability will be conducted at baseline (−1 week), mid-intervention (12 weeks), and post-intervention (24 weeks). Additionally, 20 participants from each group will undergo fMRI scans before and after the intervention to explore brain functional and structural changes relating to emotion, attention, cognition, motor skills, and sensory perception.

**Discussion:**

This study aims to contribute valuable insights into the effectiveness of Qigong practice, specifically Baduanjin, in enhancing emotional regulation, attention, and cognitive functions in acupuncturists and to investigate the neuroimaging mechanisms behind these effects.

**Ethics and dissemination:**

Approved by the Sichuan Regional Ethics Review Committee on Traditional Chinese Medicine (No. 2023KL − 118) and adhering to the Declaration of Helsinki. Results will be shared through policy briefs, workshops, peer-reviewed journals, and conferences.

**Clinical trial registration**www.chictr.org.cn, ChiCTR2300076447.

## Background

Acupuncture, now prevalent in 196 countries and regions worldwide, has undergone rapid development and is increasing global acceptance (Liu, 2023). This traditional intervention, deeply rooted in diagnostic assessments, acupoint selection, and adherence to medical guidelines, requires acupuncturists to maintain unwavering focus and emotional calm. Such qualities are crucial for effective treatment, as highlighted in the foundational text of Traditional Chinese Medicine, Huangdi Neijing (Fu and Yang, 2019).

Qigong, a longstanding practice among Chinese acupuncturists, emphasizes the regulation of the body, breath, and mind. Within the diverse array of Qigong forms, Baduanjin emerges as a particularly popular method. Distinguished by its combination of deliberate movements, focused attention, deep breathing, and relaxation, Baduanjin is recognized as a safe and effective form of aerobic exercise. It adheres to the established laws and theories of Qigong in traditional Chinese medicine (Koh, 1982; Fang et al., 2021), with a distinctive focus on harmonizing the mind and body (An et al., 2008).

Recent scientific studies have illuminated the extensive health benefits of Baduanjin across various demographic groups and health conditions. Clinical research has revealed Baduanjin’s potential to bolster physical health, enhance life quality, and improve emotional well-being in healthy individuals (Cheng, 2015; Liao et al., 2015; Zou et al., 2018a). Systematic reviews have demonstrated its effectiveness in reducing symptoms of depression and anxiety in those with physical or mental health challenges (Zou et al., 2018b). Moreover, Baduanjin has shown efficacy in enhancing cognitive functions, including memory and executive function, particularly in older adults with mild cognitive impairment (Tao et al., 2019). Additionally, it has been linked to positive outcomes in various conditions, such as Parkinson’s disease (Liu et al., 2019; Xia et al., 2019), hypertension (Xiong et al., 2015), chronic obstructive pulmonary disease (Liu et al., 2018), type 2 diabetes (Wen et al., 2017), low back pain, and knee osteoarthritis (An et al., 2013; Li et al., 2019).

While many skilled acupuncturists incorporate Traditional Chinese Qigong practices to refine their concentration and emotional regulation, thus improving their acupuncture techniques and effectiveness (Zou et al., 2021), rigorous, evidence-based medicine trials are lacking to substantiate the efficacy of these practices. Moreover, the underlying mechanisms driving these benefits remain largely unexplored.

Neuroimaging technologies, including functional magnetic resonance imaging (fMRI), positron emission tomography (PET), electroencephalography (EEG), and functional near-infrared spectroscopy (fNIRS), have revolutionized the study of neural activity. Among these, fMRI stands out for its convenience, non-invasive nature, and comprehensive brain coverage. This has led to its widespread application in neurology, psychiatry, and cognitive psychology research (Rashid and Calhoun, 2020). Prior neuroimaging studies have identified distinct differences in sensory-motor specialization (Dong et al., 2014, 2015) and emotional control (Dong et al., 2013) between acupuncturists and non-acupuncturists, likely attributable to the unique skills acupuncturists develop in clinical settings.

Given this background, we hypothesize that Baduanjin practice may significantly enhance emotion regulation, cognitive functioning, finger sensation, and motor skills. The aim of this clinical neuroimaging study is to assess the impact of long-term Baduanjin practice, regular aerobic exercise, and a waiting-list control group on these functions. Furthermore, the study intends to explore the neural mechanisms underpinning these effects.

### Objective

(1) To evaluate the effects of Baduanjin exercises on emotion control, attention, and cognitive abilities compared to regular aerobic exercise and a control group on a waiting list.(2) To visually demonstrate the impact of Baduanjin exercises on brain function related to emotion regulation and its influence on associated networks, including attention, cognitive abilities, motor skills, and sensory functions.

### Hypotheses

Acupuncturist Long-term participation in Qigong will differ significantly from aerobic and waiting exercises in terms of emotional cognition and attention.

*H1*: Long-term participation in Qigong, specifically Baduanjin, is expected to markedly improve acupuncturists’ capabilities in emotion regulation, attention, and cognition.

*H2*: It is also anticipated to cause observable changes in the structure and functional dynamics of specific brain regions.

## Methods and analysis

### Study design

This single-center, parallel randomized controlled clinical trial will enroll 99 eligible subjects from Chengdu University of Traditional Chinese Medicine.

### Participants

The trial aims to recruit 99 participants from the School of Acupuncture and Tuina at Chengdu University of Traditional Chinese Medicine. Recruitment will be facilitated through various channels, including campus radio broadcasts, on-campus advertising, and online platforms.

They will be randomly assigned in a 1:1:1 ratio to the Baduanjin group, the aerobic exercise group, or the waiting-list group.

### Procedure

The study’s physical and psychological outcomes will be evaluated at three key intervals: one week before the intervention, at 12 weeks (mid-intervention), and at 24 weeks (post-intervention). Additionally, 20 individuals from each group will be selected randomly for pre-and post-intervention fMRI scanning. The study’s process and timeline are depicted in Figure 1 and Table 1.

**Figure 1 fig1:**
[figure not shown]
The roadmap of the study process.

**Table 1 tab1:** Schedule of the trial.

Items			Study process			
			Baseline period	Intervention period (0-24 week)		
Time point			1-week	0-week	12-week	24-week
*Screening and preparation*						
Informed consent			√			
Randomization and allocation			√			
Coaching seminar			√			
*Intervention*						
Baduanjin group				√	√	√
Aerobic exercise group				√	√	√
Waiting group				√	√	√
*Clinical outcomes measurement*	*Primary outcomes*	*Emotional control*				
		SPQ	√		√	√
		IRI	√		√	√
		POMS	√		√	√
		CD-RISC-25	√		√	√
		ECS	√		√	√
		*Attention control*				
		Schulte table software	√		√	√
		*Cognitive function*				
		CFS	√		√	√
	*Secondary outcomes*	*Hand motor function*				
		Hand grip strength	√		√	√
		Finger pinch strength	√		√	√
		Purdue pegboard	√		√	√
		*Hand sensory*				
		Touch-Test	√		√	√
		Two-Point test	√		√	√
		Acupuncture test	√		√	√
*Image scanning*						
fMRI			√			√
*Subject safety*						
Laboratory examination			√			
AEs				√	√	√

This study includes a 1-week advance baseline period and a 24-week intervention period for each participant.

SPQ, the Situational Pain Questionnaire; IRI, the Interpersonal Reactivity Index; POMS, the profile of Mood States; CD-RISC-25, the Chinese version of the Connor-Davidson Mental Toughness Scale; ECS, the Emotional Contagion Scale; CFS, the Cognitive Flexibility Scale; AEs, Adverse events. Laboratory test: including routine examination of blood, urine, and stool, blood biochemical test (including liver and kidney function), and electrocardiogram examination.

#### Inclusion criteria

Subjects will be recruited if they:

Be aged between 18 and 25 years;Be right-handed;Provide informed consent;Be a full-time acupuncture student with completed courses in acupuncture and moxibustion (45 h), meridians and acupoints (84 h), and possess clinical practice experience, as evidenced by passing semester examinations.

#### Exclusion criteria

Subjects will be exclusion if they:

Have chronic pain conditions, a history of head trauma with loss of consciousness, or intellectual disabilities;Are unable to comply with project requirements;Suffer from psychiatric, respiratory, cardiovascular, or renal illnesses;Are pregnant, planning a pregnancy, or lactating;Have a history of alcohol or substance abuse/dependence;Show evident organic lesions or severe cranial anatomical asymmetry;Have contraindications for MRI, such as claustrophobia or non-removable metal in the body;Engage in long-term regular practice of Qigong, martial arts, dance, aerobics, sparring, or taekwondo.

#### Sample size estimation

This preliminary exploratory clinical randomized controlled neuroimaging trial is informed by similar studies and the minimal sample size guidelines for clinical investigations (Yuen et al., 2021). Accounting for a potential 10% dropout rate, we aim to enroll 33 subjects per group, totaling 99 subjects across three groups. A previous neuroimaging study (Szucs and Ioannidis, 2020) indicates that an imaging sample size of more than 15 per group yields reliable and consistent results. Therefore, 20 subjects from each group will be randomly selected for functional magnetic resonance imaging (fMRI) scans.

### Subjects safety

Prior to the trial, a detailed evaluation of the subjects’ medical histories will be conducted. Routine examinations, including blood, urine, and fecal tests, will be performed before and after the intervention. Electrocardiography tests will also be administered pre-intervention. All adverse events following the intervention will be descriptively documented in the Case Report Form (CRF). Severe adverse events will be closely monitored, managed, and followed up, with immediate reporting to the Ethics Committee within 24 h of occurrence (Harriss et al., 2019).

### Randomization and blinding

Given the nature of this trial, blinding of subjects and exercise coaches is not feasible. The random allocation sequence will be generated using SPSS 26.0 software (SPSS Inc., Chicago, IL, United States) to assign treatments. Allocation will be concealed in sealed, opaque envelopes, opened by the subject management center in sequential order according to subject serial numbers. Subjects will then be allocated to the respective trial groups and adhere to the exercise intervention protocol. A dedicated project manager, separate from the exercise coaches, will oversee the random allocation sequence and the blinding process. The project manager and exercise coaches will not participate in outcome assessments, and likewise, outcome assessors and the statistician will not be involved in subject screening or allocation. The study ensures a strict delineation of roles among researchers, operators, and statisticians.

## Intervention

### Intervention regimen

Previous research (Health Qigong Management Center of General Administration of Sport of China, 2003) indicates that participants in both the Baduanjin and aerobic exercise groups engaged in 60-min sessions, three times weekly, for a duration of 24 weeks. Subjects’ energy expenditure and heart rate (HR) during training will be monitored using a Polar HR monitor (Mio Sports SD).

### Baduanjin group

In accordance with the Health Qigong Management Center of General Administration of Sport of China (2003), the Baduanjin group will undergo 24 weeks of training. Each session will last 60 min, comprising a 10-min warm-up, 40 min of Baduanjin exercises, and a 10-min cool-down. This regimen encompasses 10 postures, including preparatory and finishing positions (Figure 2). Supervision and instruction will be provided by a senior social sports instructor with over 5 years of teaching experience. The week preceding the training will feature professional theoretical and movement instruction.

**Figure 2 fig2:**
[figure not shown]
The action pictures of Baduanjin were taken with the assistance of professionals employed by our research team. **(A)** Preparation posture. **(B)** Prop up the sky with hands to regulate the triple energizer. **(C)** Draw a bow on both sides like shooting a vulture. **(D)** Raise a single arm to regulate the spleen (Pi) and stomach (Wei). **(E)** Look back to treat five strains and seven impairments. **(F)** Sway head and buttocks to expel heart (Xin)-fire. **(G)** Pull toes with both hands to reinforce the kidney (Shen) and waist. **(H)** Clench fists and look with eyes wide open to enhance strength and stamina. **(F)** Rise and fall on tiptoes to dispel all diseases. **(J)** Ending posture.

### Aerobic exercise group

Participants in the aerobic exercise group will engage in brisk walking sessions, each lasting 60 min. This includes a 10-min warm-up, 40 min of brisk walking, and a 10-min rest period. Training duration and frequency will mirror those of the Baduanjin group. Professional coaches will guide these sessions, ensuring that exercise intensity remains within 55–75% of the participants’ reserve heart rate, consistent with Baduanjin group guidelines.

### Waiting-list group

The waiting-list group will not participate in any specific exercise regimen. Instead, they will be instructed to maintain their regular activity habits and provide monthly exercise reports.

## Outcome measurements

Outcome measurements will be conducted by trained independent assessors, and all results will be recorded, irrespective of subject completion status. The study timeline, including enrollment, interventions, assessments, and visits, is outlined in Table 1.

### Primary outcome measurement

Primary outcomes focus on attention control, cognitive function, and emotional control, assessed using various tools:

Schulte Table Software (Prokopenko et al., 2013) for evaluating concentration and attention switching.Cognitive Flexibility Scale (CFS) (López et al., 2022) for assessing cognitive flexibility.To evaluate the capacity for regulating emotions: Emotional Contagion Scale (ECS) (Doherty, 1997) for measuring susceptibility to others’ emotions.

### Secondary outcome measurement

Secondary outcomes involve additional emotion regulation measures and hand function assessments:

Situational Pain Questionnaire (SPQ) (Stangier et al., 2021): A self-report tool with robust psychometric properties. Interpersonal Reactivity Index (IRI) (Escrivá, 2004): Commonly used for empathy assessment. Profile of Mood States (POMS) (Shahid et al., 2011): Evaluates affective changes during the assessment period. Chinese version of the Connor-Davidson Mental Toughness Scale (CD-RISC-25) (Connor and Davidson, 2003): A brief self-rated tool for quantifying resilience.

Hand motor function is assessed using the Jamar Hand Grip Strength Meter (Wiegert et al., 2022), Jamar Finger Pinch Strength Meter (King, 2013), and Purdue Pegboard Test for manipulative dexterity (Tiffin and Asher, 1948). Hand sensory function is evaluated using the Touch-Test Mono-filament Test (Kaluga et al., 2014), Two-Point Discrimination Sensory Test (Dellon et al., 1987), and a Composite Acupuncture Test developed by the researchers (see Table 2 for details).

**Table 2 tab2:** Instructions for the acupuncture test.

[figure not shown]	[figure not shown]

Molds: five human silicone molds that tested by a professional senior acupuncture physician, the hardness of the mold was simulated for the corresponding human skin, fat, muscle, tendon, and skeletal muscle tissue, respectively.

Test items: Sensory test, subjects will acupuncture the center of the mold circle and rank the mold hardness within 15 s in blinding. Accuracy test, the right circular sticker was applied to the mold’s surface, and subjects were instructed to puncture the sticker’s center. The measurement was taken of the separation between the sticker’s pinhole and the circle’s center. Depth test, the subjects needled the mold with the same hardness such as muscle layer, and the distance of the needle body was measured.

### fMRI outcome measurement

MRI data will be acquired using a 3.0-T GE MR750 scanner (GE 3.0 T MR750, Wauwatosa, WI, United States) with an eight-channel phase-array head coil at the University of Electronic Science and Technology of China’s MRI Center.

Scanning parameters include: Structural imaging: Repetition time (TR)/Echo time (TE) = 1900 ms/2.26 ms; slice thickness = 1 mm; 30 slices; matrix size = 128 × 128; field of view (FOV) = 256 × 256 mm. BOLD-fMRI: TR/TE = 2000 ms/30 ms; flip angle = 90°; 30 slices; matrix size = 128 × 128; FOV = 240 × 240 mm; slice thickness = 5 mm; total volume = 240. DTI: TR/TE = 6,800 ms/93 ms; FOV = 240 × 240 mm; matrix size = 128 × 128; slice thickness = 3 mm; two diffusion-weighted sequences with *b* = 1000s/mm^2^ and *b* = 0 across 30 non-collinear directions.

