### Neuroimaging data analysis

The fMRI data will be conducted pre-processing in accordance with SPM12^1^ and MATLAB 2013b (MathWorks, Inc., Natick, MA, United States).

Data preprocessing will include discarding the first 5 time-points due to magnetic saturation effects, slice timing, head-motion correction, spatial normalization in Montreal Neurological Institute (MNI) space (resampled at 3 mm × 3 mm × 3 mm voxel size), filtering, and spatial smoothing with an 8-mm FWHM Gaussian kernel.

After preprocessing, the amplitude of low-frequency fluctuation (ALFF), fractional ALFF (fALFF), regional homogeneity (ReHo), functional connectivity (FC), and other brain functional parameters will be analyzed. The 3D-T1 data will be processed using voxel-based morphometry in SPM12 and the CAT12 toolbox in MATLAB (Ashburner and Friston, 2000). DTI data will undergo preprocessing and analysis with the Functional Software Library v4.1.9.^2^ Fractional anisotropy (FA) indices and mean diffusivity (MD) maps will be derived after correcting for head motion and eddy currents in DTI images, followed by tensor model fitting. Correlation analyzes will involve Pearson correlation coefficients between clinical and fMRI data, primarily focusing on functional and structural changes in brain regions associated with emotions, attention, motor skills, and sensory perception.

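### The structural MRI is specified as 30 slices of 1 mm, a 30-mm slab that cannot support the voxel-based morphometry planned on it

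*Protocol article*

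**What the plan says.** Under fMRI outcome measurement, the protocol article gives the geometry of the structural scan as "slice thickness = 1 mm; 30 slices; matrix size = 128 × 128; field of view (FOV) = 256 × 256 mm". The BOLD line that follows reads "flip angle = 90°; 30 slices; matrix size = 128 × 128; FOV = 240 × 240 mm; slice thickness = 5 mm". The diffusion scan is listed separately, with 3-mm slices and no slice count.

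Under Neuroimaging data analysis, the use of the structural scan is stated: "The 3D-T1 data will be processed using voxel-based morphometry in SPM12 and the CAT12 toolbox". The same section plans FA and MD maps from the diffusion data, and ALFF, fALFF, ReHo and functional connectivity from the BOLD data. Its correlations with clinical measures focus on regions serving emotion, attention, motor skill and sensory perception.

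The hypothesis behind these analyses is H2: "It is also anticipated to cause observable changes in the structure and functional dynamics of specific brain regions". Twenty participants per group are scanned, and Table 1 places imaging at baseline and week 24 only.

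**The concern.** The article fixes an acquisition and an analysis that do not fit together. VBM segments tissue across the brain and normalises each brain to a template, so it needs a volume that covers essentially the whole brain. The structural line gives "slice thickness = 1 mm; 30 slices", which is a thin slab. The regions of interest are spread over the brain and would not all lie inside it.

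If the scanner were set as written, no usable grey-matter result would come from VBM at either visit. The baseline loss would be permanent, because a pre-intervention scan cannot be repeated once training has started. If the scanner already runs a whole-brain sequence, nothing is lost in the data, but the published specification is wrong and another group could not reproduce it.

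**Working it through.** **Inputs**

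| Quantity | Structural scan | BOLD scan |
|---|---|---|
| Slices | 30 | 30 |
| Slice thickness | 1 mm | 5 mm |
| Matrix | 128 × 128 | 128 × 128 |
| Field of view | 256 × 256 mm | 240 × 240 mm |
| Gap between slices | not stated | not stated |

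All figures come from the section on fMRI outcome measurement. The article states no total coverage, so there is no figure of its own to reproduce.

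**Coverage.** Coverage = slices × thickness + (slices − 1) × gap. With gap = 0:

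- Structural: 30 × 1 = 30 mm.
- BOLD: 30 × 5 = 150 mm.
- Ratio: 30 / 150 = 20%.

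A gap in the BOLD scan would lengthen the BOLD slab and lower this ratio. Only a gap in the structural scan would raise it.

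**Comparison with the brain.** The documents give no brain size, so I assume an extent E of 120 to 180 mm along the slice direction. The gap that 30 one-millimetre slices would need is (E − 30) / 29. The thickness that 30 contiguous slices would need is E / 30.

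| Assumed E | Share covered by 30 mm | 1-mm slices needed | Gap needed with 30 slices | Thickness needed with 30 slices |
|---|---|---|---|---|
| 120 mm | 25% | 120 | 3.1 mm | 4 mm |
| 150 mm | 20% | 150 | 4.1 mm | 5 mm |
| 180 mm | 17% | 180 | 5.2 mm | 6 mm |

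**Can any reading rescue the figure?** Gaps of 3 to 5 mm between 1-mm slices do not fit a 3D T1 volume, which is contiguous. Thicker slices contradict the stated 1 mm. Changing the slice orientation does not help, because 30 mm is short of the whole assumed range. The article mentions no partial-brain acquisition and gives no other structural slice count.

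**Possible origin.** The slice count and the matrix are the same in both lines. The in-plane pixel is 256 / 128 = 2.0 mm for the structural scan and 240 / 128 = 1.875 mm for BOLD. A carry-over from the BOLD line would explain the slice count, and possibly the matrix. This is an inference.

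**Scans concerned.** 20 per group × 3 groups = 60 participants, and 60 × 2 visits = 120 structural scans.

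**The case against.** The best defence is that this is a reporting slip in a condensed article. The analysis section speaks of 3D T1 data and names standard VBM software, which suggests that an ordinary volumetric scan is intended. The scanner's stored sequence is not shown and may well be right. The section on quality control of imaging tests also provides for professional review of the data after scanning. That review is aimed at artefacts and distortion, but a 30-mm slab would be hard to overlook.

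Much of this stands. It makes loss of the VBM data a worst case, not the expected result. It does not make the stated figure right: the article gives a specific slice count, and that count conflicts with its own analysis. A review after scanning also comes too late to prevent the first faulty scan.

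A reader might infer more than the documents support:

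- **That the whole structural half of H2 fails.** It does not. FA and MD from the diffusion scan also address structure and have their own parameters.
- **That the functional analyses fail too.** The listed preprocessing steps include normalisation to MNI space but no coregistration to the T1 scan, so damage to the BOLD analyses would be an assumption.
- **That 2-mm pixels with 1-mm slices are an error in themselves.** They are unusual, but they contradict nothing in the article.
- **That 150 slices is a minimum.** That number only matches the BOLD slab, and it assumes the same orientation and no BOLD gap.

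**Conclusion.** The specification is wrong as written. Thirty slices of 1 mm give 30 mm, which is 20% of the trial's own 150-mm BOLD slab and 17–25% of an assumed brain extent of 120–180 mm. The VBM planned under Neuroimaging data analysis could not be carried out on such data. The consequence is confined to the VBM part of the structural test of H2.

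This should be fixed, but it does not threaten the trial. Imaging is not among the listed primary or secondary outcomes, the article calls the trial exploratory, and neither the randomisation nor the sample size depends on this number.

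The 20% figure assumes no gaps in either scan. The 17–25% range rests on the assumed brain extent. That VBM needs near-complete brain coverage follows from the method; the article does not itself use the term whole-brain for it.

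**What to change.** Reconcile the structural slice count and matrix under fMRI outcome measurement with the sequence stored on the scanner and with the VBM plan. State a contiguous 3D acquisition that covers the whole brain. At 1-mm thickness this is on the order of 120–180 slices for the assumed extent; 150 would match the BOLD slab. Give the matrix and voxel size that are actually used, and confirm or correct "matrix size = 128 × 128; field of view (FOV) = 256 × 256 mm".

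Do this before the first baseline scan, and run one pilot volume through CAT12 to confirm that it segments. The cost is nil if the scanner already holds such a sequence, because only the text changes. Otherwise it is some added scan time at each of the two imaging visits.
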